**Abstract**

**Background:** The pandemic of Coronavirus Disease 2019 (COVID-19) affects the whole health system and the global economy. One of the reasons is that there is unfortunately little information about disease management especially in critically ill patients of COVID-19. A significant percentage of these patients develop acute respiratory distress syndrome (ARDS) due to cytokine storm. We hypothesize early administration of corticosteroids alone or in combination with intravenous immunoglobulin (IV-IG) and interferon-beta can improve the outcome of the disease.

**Methods:** This is a phase two multi-center randomized controlled trial (RCT) with three parallel arms (1:1:1). In each arm, 35 subjects will be enrolled. Each eligible subject will be allocated in an intervention group or control group with a simple randomization method. The control and two other groups will be received the standard treatment for COVID-19. The intervention 1 group will be also received dexamethasone, at the first 24 hours' time of admission, and will be continued base on the improvement of the level of SpO2. Another group will be received dexamethasone for the first three days. In the groups of 1 and 2 interventions, IV-IG and interferon-beta will be supported the treatment after 24 or 72 hours of dexamethasone prescription, respectively. The cases will be followed up for one month after discharge. The primary outcome will be an improvement in the level of SpO2 of more than 90%. The secondary outcomes will be the hospital length of stay, intubation status, and the percentage of patients who are free of mechanical ventilation, the mortality rate during hospitalization, and one month after the admission time.

**Discussion:** There are many questions about the treatment and effectiveness of all used drugs in this COVID-19 situation. But, at present, there is no safety and effectiveness data from RCTs on corticosteroids in combination with IV-IG and interferon-beta against COVID-19. Cytokine storm and inflammatory mediators are two main suspects for ARDS in these patients. Theoretically, corticosteroids could help to reduce the incidence of ARDS and consequently the mortality rate. However, the aggregation of the results of different studies indicates an improvement in disease outcomes using corticosteroids in critically ill patients. This trial will try to show the effectiveness or disadvantages of corticosteroids, IV-IG, and interferon-beta administrations in critically ill COVID-19.

**Trial registration:** IRCT20120225009124N4 version 1

**Keywords:** Coronavirus; COVID-19; Randomized Controlled Trial; Protocol; Corticosteroids; Patients management; Inflammation

**Administrative information**

Note: the numbers in curly brackets in this protocol refer to SPIRIT checklist item numbers. The order of the items has been modified to group similar items (see <http://www.equator-network.org/reporting-guidelines/spirit-2013-statement-defining-standard-protocol-items-for-clinical-trials/>).

| Title {1} | Efficacy of Different Methods of Combination Regimen Administrations Including Dexamethasone, Intravenous Immunoglobulin, and Interferon-Beta for Treatment of Severe COVID-19 Patients: Study Protocol for a randomized controlled trial |
| --- | --- |
| Trial registration {2a and 2b}. | This trial was registered in the Iranian Registry of Clinical Trials (IRCT) system. This is a Primary Registry in the WHO Registry Network set up with help from the Ministry of Health and Medical Education (MOHME) and hosted by Iran University of Medical Sciences (IUMS).  Registry website: <https://www.irct.ir/> |
| Protocol version {3} | IRCT20120225009124N4 version 1; Registration date: April 2 2020. |
| Funding {4} | The Golestan University of Medical Sciences, Iran supported the present RCT (grant no. 111542). |
| Author details {5a} | Golestan Rheumatology Research Center, Golestan University of Medical Sciences, Gorgan, Iran; Infectious Diseases Research Center, Golestan University of Medical Sciences, Gorgan, Iran; Golestan Research Center of Gastroenterology and Hepatology, Golestan University of Medical Sciences, Gorgan, Iran; Clinical Research Development Center (CRDC), Sayad Shirazi Hospital, Golestan University of Medical Sciences, Gorgan, Iran; Cancer Research Center, Golestan University of Medical Sciences, Gorgan, Iran; AND Clinical Research Development Unit (CRDU), 5th Azar Hospital, Golestan University of Medical Sciences, Gorgan, Iran. |
| Name and contact information for the trial sponsor {5b} | Name of sponsor organization is the Golestan University of Medical Sciences, Gorgan, Golestan, Iran.  The full name of the responsible person is [name].  [contact]; Email: [contact] |
| Role of sponsor {5c} | The funders had no role in the design of the trial, the intervention procedures, data collection, evaluation and analysis, and selection of a journal for submitting the final version of the present protocol. |

**Introduction**

**Background and rationale {6a}**

Coronavirus Disease 2019 (COVID-19) appeared in Wuhan, Hubei, China in December 2019 and the disease spread rapidly around the world since January 2020 and became a pandemic in March 2020. Severe acute respiratory syndrome coronavirus 2 (SARS-CoV-2) (formerly known as 2019-nCoV) is the etiology agent of the disease (1). The COVID-19 infected more than 6700000 individuals all around the world and more than 390000 of them have died, which makes an extraordinary time for our planet. The disease has put a lot of pressure on health care systems, because the number of patients is increasing exponentially, especially in the early days of the spread of infection in each area. Besides, there is no still vaccine or proven effective anti-viral therapy for the disease to help the clinicians to manage it. There is little information about disease management in critically ill patients. The World Health Organization (WHO) and the United States Center for Disease Control and Prevention (CDC) are still working and researching on the best guidance for the management of COVID-19 (2).

Currently, the Ministry of Health and Medical Education (MOHME) of Iran recommends a combination of different antiviral drugs including KALETRA (lopinavir and ritonavir), atazanavir and ritonavir with interferon-beta for the treatment of COVID-19 cases along with supportive therapy. However, this guideline emphasizes that the therapeutic effects of these drugs have not been conclusively proven [Available from: http://dme.behdasht.gov.ir].

Based on some evidence, a significant percentage of COVID-19 patients develop acute respiratory distress syndrome (ARDS). In this regard, the cytokine storm can be one of the most dangerous complications of the clinical onset (3). Furthermore, in the majority of these severe cases, similar to SARS, lymphopenia, and excessive inflammatory responses of the immune system have been reported, which are the main causes of lung tissue damage, and death of patients (4,5). Therefore, it seems that anti-inflammatory drugs including corticosteroids can be used to effectively reduce the effect of this cytokine storm in these patients and the rising mortality (3,4). Corticosteroids including dexamethasone can control the production and the amount of release of some cytokines including interleukin (IL)-1, IL-6, IL-8, IL-12, and Tumor necrosis factor-alpha (TNFα) (4,6). It should be noted that anti-inflammatory drugs including corticosteroids are not routinely recommended in viral infections, because they have several side effects and can reduce the power of the immune system and should be used with caution in people with the viral infections. However, some previous studies showed that corticosteroids can be helpful in critically ill patients with the hyper-inflammation situation in SARS-CoV (3,6,7).

Corticosteroids can be used with some other medications including intravenous immunoglobulin (IV-IG) to reduce the side effect of them and control the cytokine storm. IV-IG can regulate immune system activity. Results of various studies highlighted that IV-IG compensated the side effect of corticosteroids on the immune system (3,8). Interferon-beta is another factor that has anti-viral and anti-inflammation effects, which leads to being a drug candidate for COVID-19 (9).

Currently, the combinations of three categories of drugs including corticosteroids, IV-IG, and interferon-beta are used experimentally by clinicians in some centers of COVID-19 patients. in this regard, some unpublished data showed some effectiveness in the improvement of cases. However, the best time to start prescribing this regimen and the best candidate for patients to use these drugs are two of the main questions that are still unclear. In a study in China in 2020, Wang et al. reported that the administration of methylprednisolone with a dosage of 1-2 mg/kg/d for 5-7 days was effective in cases with severe COVID-19 pneumonia. These cases had a faster improvement of SPO2 and shorter hospital stay days compared to the control group (10). Moreover, in another study, two doses of dexamethasone were used in infected pigs with porcine respiratory coronavirus and the laboratory results suggested that the drug may effectively reduce the inflammatory response in the acute phase of infection (11). However, the results of the effectiveness of these drugs in different studies have been reported differently and have not yet been fully determined. The reason for this may be due to differences in the type and timing of medication. Due to this, we designed a trial to test a hypothesis that early administration of dexamethasone in combination with IV-IG and interferon-beta can reduce the effect of cytokine storm in the critically ill patient of COVID-19.

**Objective {7}**

The primary study objective is to analyse the efficacy of different methods of dexamethasone in combination with IV-IG and interferon-beta to treat critically ill COVID-19 patients.

**Trial design {8}**

This is a phase two randomized controlled trial (RCT) with three parallel arms (1:1:1 ratio). Participants will be recruited in three arms including control, intervention 1, and intervention 2 arms. The participants will be allocated in the study arms using a simple randomization method.

**Methods: Participants, interventions, and outcomes**

**Study setting {9}**

The study will be a multi-center study and conducted in hospitals of Golestan province, Iran. Qualified patients admitted to the hospitals will be included in the study. Data on demographic and risk factors will be collected using a questionnaire. Clinical data, as well as laboratory data and imaging results, will be collected from the hospital information system (HIS). Clinical data will be symptoms, systolic and diastolic blood pressure, chronic medical illnesses, and heart and respiratory rates. Important laboratory data will be complete blood count (CBC), coagulation factors, and blood chemistry characteristics.

**Eligibility criteria {10}**

The following eligibility criteria will be set for participants:

Inclusion criteria: age 18-70 years old; proven of severe COVID-19 cases.

Exclusion criteria: the need for intubation; allergy, intolerance, or contraindication to any study drug including dexamethasone, IV-IG, and interferon-beta; pregnancy or lactation; known HIV positivity or active hepatitis B or C.

A critically ill COVID-19 case is defined as a patient with positive RT-PCR test who have a blood oxygen saturation level (SpO2) less than 90% and respiratory rate higher than 24 per minute or have involvement of more than 50% of his/her lung when viewed using computed tomography (CT)-scan. Internal medicine, pulmonologist, and nurses will perform the interventions.

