**Intervention description {11a}**

The study subjects will be randomly allocated in three treatment arms and divided into two experimental groups (two arms: intervention 1 and intervention 2) and one control group, which will be matched for age and sex using frequency matching method (Figure 1). Each eligible patient in the control arm will be received the standard treatment for COVID-19 (a combination of antiviral drugs) and the usual standard of care according to the protocol of MOHME of Iran. If the proposed standard treatment is changed, all patients will receive a new suggestion for further treatment. Each patient in the intervention 1 group will receive the standard treatment for COVID-19 and dexamethasone, (as described below), during the first 24 hours of admission. The dexamethasone will be administrated base on the level of SpO2. If the level of SpO2 does not improve after 24 hours, IV-IG and interferon-beta will be prescribed as shown below along with dexamethasone administration. In the intervention 2 group, the administration of dexamethasone will be started at the first 24 hours of admission and will be continued until 48-72 hours and the level of SpO2 will be checked. Then, if the level of SpO2 does not improve after that time, IV-IG and interferon-beta will be prescribed as the same.

Drug dosages and duration of the regimes are stated below for each intervention group. The intervention begins with the administration of dexamethasone:

If the percentage of the SpO2 level is between 85 and 90, the dosage will be 4 mg every 12 h,

If the percentage of the SpO2 level is between 80 and 85, the dosage will be 4 mg every 8 h,

If the percentage of the SpO2 level is between 75 and 80, the dosage will be 8 mg every 12 h,

If the percentage of the SpO2 level is less than 75, the dosage will be 8 mg every 8 h.

The doses of IV-IG will be 400 mg/kg once daily for 5 days and interferon-beta will be 7 doses every other day. As a note, before the IV-IG administration, the level of IgA will be checked.

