**Outcomes {12}**

**Primary outcome**

An increase in the SpO2 level to reach more than 90% in each case, which will be assessed by the oximeter.

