**Recruitment {15}**

On each day of the study, the main internal clinical specialist will examine all newly admitted patients in each morning round and select eligible cases based on the triage, laboratory, and CT-scan findings of the patients. One of the clinical colleagues of the project will put randomly patients in three arms and explain the study plan to the patient and provides the informed consent form. The project's lead executor (the staff member responsible for study) will review the availability of all the necessary facilities and make sure that the study is done properly.

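### On its most natural reading the CT entry route has no SpO2 limit, so patients already above 90% could be randomised although the primary outcome and the dexamethasone bands do not cover them

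*Protocol*

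**What the plan says.** Protocol, Eligibility criteria {10}, lists "Inclusion criteria: age 18-70 years old; proven of severe COVID-19 cases". It then defines a critically ill case as an RT-PCR-positive patient whose oxygen saturation is "less than 90% and respiratory rate higher than 24 per minute". In the same sentence, without brackets, the CT criterion is added as an alternative: "or have involvement of more than 50% of his/her lung when viewed using computed tomography (CT)-scan". No other inclusion or exclusion criterion limits SpO2. Under Recruitment {15}, the specialist is to "select eligible cases based on the triage, laboratory, and CT-scan findings of the patients", and no SpO2 threshold is named there.

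The primary outcome (Outcomes {12}) is "An increase in the SpO2 level to reach more than 90% in each case, which will be assessed by the oximeter". It carries no condition on the baseline value.

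Intervention description {11a} sets dexamethasone by SpO2 in four bands. The highest begins "If the percentage of the SpO2 level is between 85 and 90", and nothing is listed above 90.

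The section on non-adherence and missing data {20c} puts the primary outcome under intention-to-treat. Sample size {14} gives 35 per group, two-sided 5% and 80% power, and takes the effect size from a cited study without stating it.

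**The concern.** An outcome defined as crossing a threshold works only for patients who start on the other side of it. If CT involvement alone is enough for entry, someone with, say, SpO2 94% and 55% lung involvement is eligible, and three parts of the protocol then fail to fit that patient:

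- The outcome threshold is already passed, and the protocol does not say whether this counts as success or failure.
- The assigned dexamethasone has no band.
- The patient nevertheless counts in the denominator of the primary comparison.

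Such patients carry no information on whether treatment raises SpO2 past 90%, whichever way they are scored. With 35 per arm there is little power to spare. In a multi-center trial there is a further risk that sites read the sentence differently and so enrol different populations.

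**Working it through.** **1. The two readings of the entry rule**

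- Reading A: (SpO2 <90% and respiratory rate >24) or (CT involvement >50%). The verb is repeated before the CT finding, which makes it a separate alternative.
- Reading B: SpO2 <90% and (respiratory rate >24 or CT involvement >50%). The missing brackets allow it.

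Test patient: SpO2 94%, CT 55%.

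| | Reading A | Reading B |
|---|---|---|
| Eligible | yes | no |
| Primary outcome | threshold passed at entry; scoring not stated | does not arise |
| Dexamethasone band | none (highest is 85 to 90) | does not arise |
| In intention-to-treat comparison | yes | no |

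**2. The plan's own figure**

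The 35 per group cannot be reproduced, because Sample size {14} states no rates, difference or standard deviation. I therefore worked backwards. With two-sided 5% and 35 per arm, a two-proportion test without continuity correction has 80% power for 30% vs 62.8% and for 50% vs 81.3%. These rates are my assumptions.

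**3. Dilution**

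Let f be the share of each arm above 90% at entry, also assumed, and equal across arms in expectation because of randomisation. If all of them are scored as successes, each rate p becomes f + (1 - f)p. If all are scored as failures, it becomes (1 - f)p. In both cases the difference becomes (1 - f)(p2 - p1).

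Power = Φ[(d - 1.96·se0)/se1], where d is the diluted difference, se0 = √(p̄(1 - p̄)·2/n) and se1 = √((p1(1 - p1) + p2(1 - p2))/n).

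Example, 30% vs 62.8%, f = 20%, scored as successes, n = 35:

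- Rates: 0.20 + 0.80×0.30 = 0.440 and 0.20 + 0.80×0.628 = 0.702. Difference 0.262 = 0.80×0.328.
- p̄ = 0.571, se0 = 0.1183, se1 = 0.1141.
- (0.2624 - 1.96×0.1183)/0.1141 = 0.27, so power is 61%.

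| Share f | 30% vs 62.8%, successes | 50% vs 81.3%, successes | 30% vs 62.8%, failures | 50% vs 81.3%, failures |
|---|---|---|---|---|
| 0 | 80% | 80% | 80% | 80% |
| 5% | 75% | 77% | 76% | 74% |
| 10% | 70% | 73% | 72% | 68% |
| 20% | 61% | 66% | 63% | 56% |
| 30% | 51% | 58% | 54% | 45% |

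**4. Restricting the primary set by baseline SpO2**

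The undiluted rates are kept, but n falls to 35(1 - f) per arm.

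| Share f | Patients per arm analysed | Power, both pairs of rates |
|---|---|---|
| 10% | 31.5 (average) | about 75% |
| 20% | 28 | about 70% |

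This is better than 70-73% and 61-66% with dilution (scored as successes), but it does not recover 80%.

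**The case against.** The strongest objection is that the sponsor may have meant Reading B. All four dexamethasone bands lie at or below 90%, and the primary outcome is expected of every case. Both fit a population in which everyone starts below 90%. A reader might therefore say that there is no problem, only loose punctuation. This stands in part: the documents do not prove that patients above 90% are admitted. But Reading B is not what the sentence most naturally says, and nothing else in the protocol limits SpO2. The wording needs settling either way.

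Three stronger inferences are tempting and are not supported:

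- A reader might infer that such patients meet the primary outcome on the day of entry. The outcome asks for an increase, and a patient who enters at 94% has shown none. The supportable statement is that their scoring is undefined.
- A reader might infer that the stated 80% power is broken. The protocol gives neither the share nor the rates, and does not show that 35 came from a responder proportion. At a 5% share the loss is only a few points (75-77% with successes, 74-76% with failures).
- A reader might infer bias. Randomisation spreads these patients over the arms in expectation, so what follows is a smaller difference and lower power, not a tilt towards one arm.

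**Conclusion.** The point holds as a conflict that depends on the reading. On the most natural reading, the entry rule admits patients whom the primary outcome cannot assess and whom the dexamethasone bands do not cover. The other possible reading removes the conflict. That the difference shrinks by (1 - f) follows from the definitions, provided such patients are scored alike in every arm.

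The size of the loss is illustrative only. It rests on assumed response rates, an assumed share f and a two-proportion test. With successes scoring, power falls from 80% to about 75-77% at a 5% share, 70-73% at 10%, 61-66% at 20% and 51-58% at 30%. Whether the real loss is negligible or serious depends on how many patients enter on CT alone, which the protocol does not say.

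**What to change.** 1. **Entry rule.** State which reading of the case definition applies, with brackets or as separate items, so that the entry rule matches the primary outcome.
2. **Primary analysis set.** Define it by baseline SpO2, as randomised patients whose entry SpO2 is not already above 90%, and report the others separately. Because membership is fixed before treatment, the randomised comparison is preserved.
3. **Power.** If CT-only patients are enrolled, restate the 80%. Within 105 patients the restricted set gives about 75% at a 10% share and 70% at 20%, under the assumed rates.
4. **Reconciliation.** The sponsor must reconcile the case definition with the dexamethasone bands in Intervention description {11a}. Patients above 90% have no band, and adjacent bands share the values 80 and 85, so two regimens apply at each. No dose or clinical rule is proposed here.

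**Cost.** Changes to eligibility or analyses need ethics committee approval and submission to the registry (amendments section {25}). By Trial status, recruitment ran from April 18 and was expected to end on June 19 2020, so a clarified entry rule cannot affect patients already enrolled. The analysis set can be applied to them unchanged, from their entry SpO2; its price is the smaller number analysed.

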**Who will take informed consent?** **{26a}**

The potential trial participants will sign the informed consent form if they have decision-making capacity. In the situation of the participants are unable to fill out the form, an independent clinician will confirm in writing that the participant cannot fill out the form. Therefore, her/his authorized family will be informed of the study and will be told all the advantages and disadvantages of the study and they will have the free right to include their patient to the study. Whenever the patient gains his ability and consciousness to decide, she/he will be notified of the nature of the study and has the option to stay in the study or withdraw from the study. Based on the request of participants all collected data will be deleted.

**Additional consent provisions for collection and use of participant data and biological specimens {26b}**

There is no application to our trial.

**Interventions**

**Explanation for the choice of comparators {6b}**

Despite all the efforts of the international community, there is still no standard protocol for the treatment of COVID-19. High-quality RCTs can help to set up an effective treatment protocol for the disease. According to the WHO (12) recommendation, all participants will have the best available supportive care with full monitoring.

